#### 7.2.1. Grading adverse events

When grading adverse events, each event is given the grade closest to the defined grades 0–4. In addition, if a specific treatment is described for a grade, grade it based on its clinical necessity. For example, when the patient's pleural fluid is increasing and the patient refuses oxygen inhalation and chest drainage despite these being indicated in this situation. In these cases, the grade should be assigned based on the medical determination of what should be done, not what was actually done.

#### 7.2.2. Causal relationship between adverse events and treatment

When determining cause and effect relationships between adverse events and treatment, these are classified into five categories: “definite, probable, possible, unlikely, and not related.” A determination of any one of “definite, probable, possible” is defined as “causality present,” and a determination of “unlikely, not related” is defined as “causality absent” (see: Table 7.2.2).

If, based on the adverse event's grade, the adverse event is classified as a serious adverse event for which there is an obligation to provide an emergency report as defined in “10.1. Serious adverse events and events subject to emergency reports”, it should be reported to the Study Representative Physician in accordance with “10.2. Requirements and procedures for reporting to the Study Representative Physician.”

Table 7.2.2 Determination criteria for causal relationships between adverse events and treatment

|                                       | Determination | Rationale for determination                                                                                                                                                                                                                                                                                                                         |
|---------------------------------------|---------------|-----------------------------------------------------------------------------------------------------------------------------------------------------------------------------------------------------------------------------------------------------------------------------------------------------------------------------------------------------|
| Cause and effect relationship present | Definite      | The AE is clearly related to the intervention
It is clear that the adverse event was caused/made more severe by the protocol treatment, and it is determined that there is little possibility of being due to exacerbation of the underlying disease or by other factors (comorbidities, other medications/treatments, coincidence)              |
|                                       | Probable      | The AE is likely related to the intervention
The adverse event is unlikely to have occurred/been made more severe as a result of exacerbation of the underlying disease or by other factors (comorbidities, other medications/treatments, coincidence), and the possibility of being due to the protocol treatment is determined to be high      |
|                                       | Possible      | The AE may be related to the intervention
It is more plausible to consider that the adverse event is caused/made more severe by protocol treatment, and while it might be due to exacerbation of the underlying disease or by other factors (comorbidities, other medications/treatments, coincidence), that possibility is determined to be low |
| Cause and effect relation-            | Unlikely      | The AE is doubtfully related to the intervention
Even though the adverse event could be considered to be caused/made more severe by protocol treatment, it is determined more likely to be due to exacerbation of the underlying disease or other factors (comorbidities, other                                                                  |

|                |             |                                                                                                                                                                                                                                                                                                                              |
|----------------|-------------|------------------------------------------------------------------------------------------------------------------------------------------------------------------------------------------------------------------------------------------------------------------------------------------------------------------------------|
| ship
absent |             | medications/treatments, coincidence)                                                                                                                                                                                                                                                                                         |
|                | Not related | The AE is clearly NOT related to the intervention
The adverse event is apparently caused/made more severe by exacerbation of the underlying disease or other factors (comorbidities, other medications/treatments, coincidence), and it is determined that there is no possibility of being due to the protocol treatment |

## 8. Evaluation parameters, clinical testing, and evaluation scheduling

### 8.1. Pre-enrollment evaluation parameters

#### 8.2. Pre-enrollment evaluation parameters (any time before enrollment)

The results and findings of tests conducted prior to obtaining consent will also be available as data.

- 1) Sex
- 2) Age (Date of birth)
- 3) Height, body weight (carried out within 14 days before enrolment in children under 15 years of age)
- 4) Medical treatment history
  - Operation history (any surgery at the primary site, any surgery for metastasis/recurrent disease)
  - Radiotherapy history (any perioperative treatment, any metastasis/recurrent disease)
  - Pharmaceutical treatment history (number of regimens, any perioperative treatments, any metastasis/recurrent disease)
- 5) History of cancer/multiple cancers (any cases, and related cancer types)
- 6) Family medical history
- 7) Cancer type
  - Histopathology exams\*: date of specimen collection, histologic classification (according to the Rare Care classification)
  - \* The timing of implementation does not matter as long as it occurs before enrollment. However, if any histopathology findings come from another facility, a pathology specimen should be obtained and a pathology diagnosis be redone at the study center.
  - Classified as first occurrence/recurrence
  - Any metastasis present/metastatic lesion
- 8) Gene panel test
  - Test name/specimen collection date/examination date
  - Genetic abnormality (related to the relevant drug selection)
    - Gene name
    - Type of abnormality: [1] gene mutation, [2] fusion gene, [3] gene deficiency, [4] gene amplification
    - [1] CDS change/amino acid change/allele frequency/differentiation of somatic cells/germ cells
    - [2], [3] Ratio of copies
    - [4] Details (if the partner gene or fusion point is known)
  - TMB-high/MSI-high
  - Misc. (Total number of exon mutations (tumor mutation burden)/total exon mutation rate/total non-exon/number of mutations/non-exon total mutation rate/total number of mutations in all regions/total mutation rate in all regions)
- 9) C-CAT number

#### 8.2.1. Tests performed within 28 days before enrollment

The results and findings of tests conducted prior to obtaining consent can also be used as data.

- 1) Imaging examination (contrast-enhanced CT or MRI: select the modality according to the cancer type)

#### 8.2.2. Tests performed within 14 days before enrollment

The following measurements are made to confirm safety.

- 1) ECOG Performance Status (PS) (If the patient is younger than 15 years of age and evaluation by ECOG is difficult, the performance status scale/score conversion table (Appendix) should be

used to confirm that the patient's performance status is equivalent to 0 or 1 on the ECOG scale.)

- 2) Hematology test: leukocyte count, differential leukocyte count (neutrophils, lymphocytes), hemoglobin, and platelet count
- 3) Blood biochemistry test: albumin, total bilirubin, AST, ALT, creatinine, sodium, potassium, LDH, calcium (albumin correction\*)

\* When serum albumin level is  $\leq 4.0$  g/dL, use the following correction(12)

Corrected calcium (mg/dL) = serum calcium level (mg/dL) + (4-serum albumin level)

### 8.2.3. Tests performed within 7 days before starting treatment

The following measurements are made to confirm safety.

- 1) ECOG Performance Status (PS) (If the patient is younger than 15 years of age and evaluation by ECOG is difficult, the performance status scale/score conversion table (Appendix) should be used to confirm that the patient's performance status is equivalent to 0 or 1 on the ECOG scale.)
- 2) Hematology test: leukocyte count, differential leukocyte count (neutrophils, lymphocytes), hemoglobin, and platelet count
- 3) Blood biochemistry test: albumin, total bilirubin, AST, ALT, creatinine, sodium, potassium, LDH, calcium (albumin correction\*)

\* When serum albumin level is  $\leq 4.0$  g/dL, use the following correction(12)

Corrected calcium (mg/dL) = serum calcium level (mg/dL) + (4-serum albumin level)

- 4) If the last imaging examination (contrast-enhanced CT or MRI: select the modality according to the cancer type) are performed more than 28 days before, it is desirable to conduct the assessment again by the start of the treatment (the assessment at the start of treatment is available).

## 8.3. Tests and evaluations during the protocol treatment period

### 8.3.1. Safety endpoints

In this study, protocol treatments are carried out with various medicines, so there is no uniform safety endpoint, but the patient's safety is evaluated with due consideration by the doctor in charge according to the description in the respective drug package insert, and tests are conducted as appropriate. The evaluations are based on "7.2 Evaluating adverse events/adverse reactions," and when they correspond to "10.1 Serious adverse events and events subject to emergency reports" they are reported to the Study Representative Physician according to "10.2 Requirements and procedures for reporting to the Study Representative Physician." Otherwise, enter into the EDC the worst grade  $\geq 2$  adverse events that have occurred from the start of treatment to 30 days after treatment discontinuation or the date of subsequent treatment initiation, whichever comes first. And the assessment of them to 30 days after treatment discontinuation or the date of initiation of subsequent treatment, whichever comes first. If adverse events are considered to be related to protocol treatment or they are severe regardless of relation to protocol treatment, follow-up will be continued as long as possible until the adverse event is considered resolved, resolved, or stable.

※Instruction of safety information shall be in accordance with the separately specified procedures.

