### 10.1. Serious adverse events and events subject to emergency reports

Serious adverse events are those that fall under any of the following. Death

- 1) Diseases, etc. that can lead to death
- 2) Diseases, etc. that require hospitalization or prolongation of hospitalization for treatment
- 3) Disability
- 4) Diseases, etc. that can lead to disability
- 5) Diseases, etc. that are serious according to 1) to 5)
- 6) Diseases or abnormalities that can lead to congenital diseases in later generations

Of these events, those that fall into any of the following categories are defined as serious adverse events for which there is an obligation to provide an emergency report. **1) Death**

- ① [1] Any death that occurs after enrollment and before starting the protocol treatment
- ② Any death during the protocol treatment or within 30 days of the last treatment (whether or not there is a causal relationship with the protocol treatment)
- ③ Death  $\geq 31$  days after the last treatment if a causal relationship with the protocol treatment cannot be ruled out (definite, probable, possible)

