### 4) Incidence of adverse events

Percentage of patients who developed each adverse event in SAS.

In addition, the frequency of the worst grade according to CTCAE v5.0-JCOG is determined for each adverse event.

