### 12.3.3. Analysis of safety secondary endpoints

Among the secondary endpoints, the safety endpoints are the incidence of adverse events. The safety analysis set is SAS for each drug cohort, and analysis for each drug cohort is performed at the time of main analysis or at the time of additional analysis of the primary endpoint thereafter. The frequencies of the worst grade for each adverse event are summed when estimating the incidence of adverse events. An accurate method (Clopper and Pearson method) based on a binomial distribution is used for 95% confidence interval estimates of the incidence. Furthermore, the safety in the FAS is to be analyzed as needed.

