#### 2) Early discontinuation due to adverse events (discontinuation due to inefficacy)

If the adverse event is outside the permissible range, patient enrollment will be temporarily suspended, and this will be reported to the Efficacy and Safety Evaluation Committee who will consider early discontinuation of the drug cohort.

Specifically, when two or more treatment-related deaths are reported for each medicine, the rate of treatment-related deaths for that medicine exceeds 2% ( $2/80 = 2.5\%$ ), and the Efficacy and Safety Evaluation Committee will deliberate on whether new patients can be enrolled and whether treatment can continue for the patients already enrolled relating to the corresponding drug cohort. Furthermore, when it is possible to enroll more than 80 patients in a drug cohort, the Efficacy and Safety Evaluation Committee will similarly deliberate when it becomes clear that the treatment-related death rate exceeds 2%. In addition, even if the above conditions are not met, the cases in which the Study Representative Physician/Study Secretariat determines that the serious adverse event occurrence profile reported in the periodic monitoring report deviates significantly from the content described in the attached document, the Efficacy and Safety Evaluation Committee will deliberate on whether new patients can be enrolled and whether treatment can continue for the patients already enrolled relating to the corresponding drug. These details are to be reported to the Medical Economics Division, Health Insurance Bureau, of the Ministry of Health, Labour and Welfare.

If a recommendation for early discontinuation is issued by the Efficacy and Safety Evaluation Committee, the Study Representative Physician/Study Secretariat will review the content of the recommendation and decide whether to proceed with early discontinuation.

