## 14. Monitoring and audits

### 14.1. Periodic monitoring

Periodic monitoring is conducted in this study to confirm that the study is being conducted safely and according to the protocol, and that data are being collected correctly. Periodic monitoring will be centralized monitoring based on the data input to eCRFs collected via EDC system, and will be performed by data management staff. In principle, it will be conducted twice per year.

The data management staff are to submit a "monitoring report" that summarizes the results of the centralized monitoring to the Study Representative Physician/Study Secretariat. Specific procedures for centralized monitoring will be determined separately in the procedure manual.

Monitoring reports serve as reference materials for periodic reporting according to the Clinical Research Act, periodic reporting on patient treatments, performance reports and reports to pharmaceutical companies providing drugs without charge (see 13.6.).

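### Section 8.3.1 words EDC entry as the alternative to emergency reporting, against other sections that expect serious events in the eCRF, and Section 7.2.1 gives no fatal grade for the worst-grade safety endpoint

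*Protocol*

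**What the plan says.** **Routing.** Section 8.3.1 deals first with events that correspond to Section 10.1: "they are reported to the Study Representative Physician according to" Section 10.2. The next sentence opens "Otherwise, enter into the EDC the worst grade" and sets a threshold of Grade 2 and a window running to 30 days after discontinuation or to the start of the next treatment. The route in 10.2 consists of report forms sent by email; it has no EDC step.

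**What takes the emergency route.** Section 10.1 covers deaths whatever their cause ("Any death during the protocol treatment or within 30 days of the last treatment (whether or not there is a causal relationship with the protocol"), Grade 4 events in the same period, and unexpected lower-grade events that need hospitalisation. It exempts a list of haematological and laboratory toxicities unless they are judged serious.

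**Grading.** Under Section 7.2.1, "each event is given the grade closest to the defined grades 0–4".

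**Endpoint and analysis.** Section 12.2.2 4) defines adverse event incidence in the Safety Analysis Set and adds that "the frequency of the worst grade according to CTCAE v5.0-JCOG is determined for each adverse event". Section 12.3.3 applies this by drug cohort: "The frequencies of the worst grade for each adverse event are summed when estimating the incidence of adverse events", with Clopper-Pearson intervals. Neither section leaves out serious events.

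**Monitoring.** Section 14.1 states: "Periodic monitoring will be centralized monitoring based on the data input to eCRFs collected via EDC system". Section 12.7.1 2) provides for committee deliberation if "the serious adverse event occurrence profile reported in the periodic monitoring report deviates significantly" from the product information.

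**The concern.** Section 8.3.1 is the only general instruction on which adverse events a site must enter in the EDC. (Section 7.2 mentions the eCRF form only for graded laboratory abnormalities in children under 15.) If its two sentences are alternatives, a site that follows them to the letter reports a death or a clinical Grade 4 event by email and does not have to enter it in the EDC. No sentence in the protocol says that an emergency-reported event is entered as well.

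The worst-grade table for each drug is a secondary endpoint, and under Section 12.3.1 results are shared with companies that provide a drug free of charge and may pursue approval. An omission here would fall on the most severe clinical events. It is a matter of data collection, so an analysis plan could not recover what sites did not enter. The 0 to 4 scale adds a second gap: a fatal event that is entered has no grade of its own, although Table 10.2.1 and the tables in 10.3.2 treat death as a level separate from Grade 4.

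**Working it through.** **Step 1. Where each type of event goes if 8.3.1 is read literally.**

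| Event, on treatment or within 30 days | Emergency route (10.1, 10.2) | EDC instruction (8.3.1) |
|---|---|---|
| Death, any cause | Yes | Not covered |
| Grade 4, not on the exempt list | Yes | Not covered |
| Grade 4, on the exempt list and not judged serious | No | Covered |
| Unexpected Grade 1 to 3 with hospitalisation | Yes | Not covered |
| Expected Grade 2 or 3 with hospitalisation | Not reported (Table 10.2.1) | Covered if 8.3.1 means only emergency-reportable events; in neither route if it means all serious events in 10.1 |
| Other Grade 2 or 3 | No | Covered |

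Listed laboratory and haematological Grade 4 events generally stay in the EDC, while clinical Grade 4 events and deaths leave it.

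**Step 2. Sections that assume the opposite.**

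- Section 8.4 has adverse events up to 30 days after treatment recorded, with no exception for emergency-reported ones.
- The calendar in Section 8.6 marks adverse events as required, again without exception.
- Section 9.2 lists seriousness, grade and outcome among the adverse event data held in the CRF.
- Section 14.1 builds the monitoring report from eCRF data, and Section 12.7.1 2) expects the serious-event profile in that report.

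These sections fit together only if serious events are in the eCRF. They contradict the literal sentence in 8.3.1.

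**Step 3. The grading scale.** Section 7.2.1 stops at 4. Sections 7.2 and 12.2.2 4) name CTCAE v5.0-JCOG as the scale. The protocol does not say which grade a fatal event receives in the worst-grade table.

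**Step 4. What an omission could do.** The protocol's one safety figure is the treatment-related-death trigger in Section 12.7.1 2): 2/80 = 0.025 = 2.5%, which reproduces. The protocol gives no expected event rates, so the counts below are assumptions. The interval is the protocol's own Clopper-Pearson method: lower limit = the 0.025 quantile of Beta(x, n − x + 1), upper limit = the 0.975 quantile of Beta(x + 1, n − x). For x = 0 the lower limit is 0 and the upper limit is 1 − 0.025^(1/n). The cohort sizes are 50 (measurable lesions only) and 80 (50 + 30).

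| Patients n | Events omitted x | Rate with the events entered (95% CI) | Rate shown if all are omitted (95% CI) |
|---|---|---|---|
| 80 | 2 | 2.5% (0.3 to 8.7%) | 0% (0 to 4.5%) |
| 80 | 4 | 5.0% (1.4 to 12.3%) | 0% (0 to 4.5%) |
| 80 | 8 | 10.0% (4.4 to 18.8%) | 0% (0 to 4.5%) |
| 50 | 2 | 4.0% (0.5 to 13.7%) | 0% (0 to 7.1%) |
| 50 | 8 | 16.0% (7.2 to 29.1%) | 0% (0 to 7.1%) |

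With 8 of 80 omitted, the interval shown would have an upper limit (4.5%) well below the actual rate (10%). The table assumes that every site reads 8.3.1 literally. If some sites enter the events anyway, the loss is smaller.

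**The case against.** The strongest reply is that the exclusive reading hangs on one word in a loosely worded paragraph, where the word could mean no more than apart from that. No section says that emergency-reported events are kept out of the EDC. The sections in Step 2 show the likely intent: a seriousness field in the CRF has little purpose if serious events are recorded elsewhere. Section 8.3.1 also points to separate safety procedures and Section 9.1.1 to an EDC input manual, neither of which is shown. On grading, CTCAE v5.0-JCOG is the named scale, the CRF records outcome, and Section 8.5 collects the date and cause of death, so a fatal event can be identified.

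Much of this stands. A reader might infer that the endpoint loses its fatal and life-threatening end outright, that fatal events must show a frequency of zero in every cohort, or that each drug will look safer than it is. The documents do not support that: other sections expect the data in the eCRF, and listed Grade 4 toxicities generally stay on the EDC route even under the literal reading.

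A reader might also infer that safety oversight is compromised. That is not supported either. The treatment-related-death trigger counts reported deaths, Section 10.5 takes emergency-reported events to the Efficacy and Safety Evaluation Committee, and Section 14.1.1 puts safety report information by drug into the monitoring report.

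The reply does not remove the conflict. The other sections show what was meant, but none tells a site to enter an emergency-reported event in the EDC, and 8.3.1 words entry as the alternative.

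**Conclusion.** The point holds as an internal contradiction in a data-collection rule that feeds a secondary endpoint. Section 8.3.1, read as written, leaves deaths, non-exempt Grade 4 events and unexpected hospitalised events out of the EDC instruction, while other sections presuppose them there. Section 7.2.1 leaves the worst-grade endpoint without a stated fatal category.

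The consequence is conditional: the per-drug worst-grade table may understate severe clinical events, to the extent that sites follow the literal wording. How many would do so, and how many events are involved, cannot be found from the protocol; the figures in Step 4 are illustrations only. The conclusion assumes that the procedures and the manual not shown do not already require both entries. If they do, what remains is a protocol text at odds with them, which still needs correcting.

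**What to change.** 1. In Section 8.3.1, replace the opening of the EDC sentence with a statement that all adverse events meeting the EDC collection rule, including those also reported under 10.2, are entered in the EDC with worst grade, seriousness and causality.
2. In Section 7.2.1, include the fatal grade, so that the scale matches the CTCAE v5.0-JCOG endpoint in 12.2.2 4).
3. Add a reconciliation of emergency reports against the eCRF to each semi-annual monitoring in Section 14.1. If the amendment comes after enrolment has begun, the first reconciliation should cover events already reported, so that missing entries can be added.

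The cost is small: two wording changes, one monitoring step, and double entry of serious events that the site has already written up. No sample size, threshold or planned figure changes.

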## **2.7. Enrollment to participate in patient-proposed healthcare services with multiple medicines**

Patients who participate in treatment within another drug cohort that is included in this study will be given the additional explanation, give consent again, and be enrolled again.

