| Adverse Events                       |           |                       |                  | ◎*7                        |                                       |
| Follow-up                            |           |                       |                  |                            | ◎                                     |

◎: Required, ○: Optional

\*1: Any time before enrollment

\*2: Within 14 days before enrollment

\*3: Select modality according to cancer type

\*4: Within 28 days before enrollment

\*5: Within 28 days before the start of treatment (including the date treatment started)

\*6: Required 16±1 weeks after the start of treatment (otherwise as appropriate)

\*7: From the start of protocol treatment to 30 days after protocol treatment discontinuation or the date of subsequent treatment initiation, whichever comes first. (assess the events to 30 days after treatment discontinuation or the date of initiation of subsequent treatment, whichever comes first). If adverse events are considered to be related to protocol treatment or they are severe regardless of relation to protocol treatment, follow-up will be continued as long as possible until the adverse event is considered

resolved, resolved, or stable.

\*8: Within 14 days after treatment discontinuation date

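### No pre-dose grade is collected for non-laboratory conditions, so symptoms already present at first dose can enter a drug's adverse event incidence and cannot be separated out later

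*Protocol*

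**What the plan says.** **Collection.** Apart from events under emergency reporting, section 8.3.1 has sites enter in the EDC the worst grade (grade 2 or higher) of "adverse events that have occurred from the start of treatment to 30 days after treatment discontinuation or the date of subsequent treatment initiation", whichever of the two end dates is earlier. Note 7 to the study calendar (8.6) gives the same window: "From the start of protocol treatment to 30 days after protocol treatment discontinuation or the date of subsequent treatment initiation, whichever comes first". The calendar's adverse event row is marked only at completion of treatment. Its cells for screening and for start of treatment are empty.

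**Endpoint.** Section 12.2.2 4) defines incidence as "Percentage of patients who developed each adverse event in SAS" and adds that "the frequency of the worst grade according to CTCAE v5.0-JCOG is determined for each adverse event". Section 12.3.3 applies this to each drug cohort: "The frequencies of the worst grade for each adverse event are summed when estimating the incidence of adverse events", with Clopper-Pearson 95% intervals. Neither section refers to a grade before dosing or to causality.

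**Baseline.** Section 8.2.2 ("Tests performed within 14 days before enrollment") and section 8.2.3 (within 7 days before treatment, introduced by "The following measurements are made to confirm safety") both require haematology, biochemistry and ECOG performance status. Neither they nor the background list in 8.2 has an item for symptoms, ongoing conditions or residual toxicity.

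**Re-enrollment.** Section 2.7 provides for patients to enter a further cohort: "Patients who participate in treatment within another drug cohort that is included in this study will be given the additional explanation", followed by new consent and a new enrollment.

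**The concern.** To say that an event developed on a drug, one must know the patient's state before the first dose. For laboratory terms the required tests can supply this. For symptoms and other non-laboratory terms, the protocol asks for nothing that could. A patient at grade 2 neuropathy both before and after dosing, and one who went from grade 0 to grade 2, can leave the same single entry.

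The population makes this more than a formality. Section 4.1 admits patients with incurable disease and any number of earlier regimens. Its criterion on earlier anti-cancer drugs states neither a length of time nor a recovery requirement for earlier toxicity, and section 6.1 leaves the interval from the previous treatment to the package insert. For a patient who moves between cohorts, the first drug's window closes on the date the second drug starts, which is the date the second drug's window opens.

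Per-drug adverse event incidence is a stated secondary endpoint, and under section 2.3.1 a company that supplies its drug free of charge may receive the safety data. If pre-existing conditions are counted, the incidence is too high by an amount that depends on case mix and on the previous drug.

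**Working it through.** The protocol states no adverse event rate and no baseline prevalence, so it has no figure to reproduce. The check compares what the endpoint needs with what is collected, and then illustrates the possible size.

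**1. Needed against collected**

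| Item | Laboratory terms | Non-laboratory terms |
|---|---|---|
| State before first dose | Haematology and biochemistry required twice (8.2.2, 8.2.3; marked required in 8.6) | No item in 8.2 to 8.2.3; adverse event cells before dosing empty in 8.6 |
| State after first dose | Worst grade, grade 2 or higher (8.3.1) | Worst grade, grade 2 or higher (8.3.1) |
| Can new or worsened be separated from unchanged? | Yes, if the pre-dose values are entered in the EDC, which the protocol does not specify | Not from what the protocol requires |

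ECOG performance status is the only clinical status measure taken before dosing, and it gives no grade for any adverse event term.

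**2. Does causality filter the count?** Section 7.2.2 grades causality in five categories, weighing underlying disease and other treatments. The definition in 12.2.2 4) does not use it, so the incidence includes events of any cause.

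**3. Possible size, on assumptions.** Let t be the true incidence of new events and b the proportion who already have the condition at grade 2 or higher at first dose. Neither is in the documents. Assume that the two are independent and that every pre-existing condition is entered as an event. Then

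apparent incidence = 1 − (1 − t)(1 − b).

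Take N = 50 + 30 = 80, the planned cohort size with and without measurable lesions, and t = 10%. Intervals are Clopper-Pearson, as in 12.3.3.

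| b | Apparent incidence | Expected count | Rounded count | 95% CI |
|---|---|---|---|---|
| 0% | 10.0% | 8.0 | 8/80 | 4.4 to 18.8% |
| 5% | 1 − 0.90 × 0.95 = 14.5% | 11.6 | 12/80 | 8.0 to 24.7% |
| 10% | 1 − 0.90 × 0.90 = 19.0% | 15.2 | 15/80 | 10.9 to 29.0% |
| 20% | 1 − 0.90 × 0.80 = 28.0% | 22.4 | 22/80 | 18.1 to 38.6% |

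With t = 0, a drug that has no effect on the term, b = 10%, 20% or 30% gives 8/80 (4.4 to 18.8%), 16/80 (11.9 to 30.4%) or 24/80 (20.3 to 41.3%).

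The result 8/80 with interval 4.4 to 18.8% appears in both sets: once with every event new, and once with none new. Without a pre-dose grade, the required entries do not distinguish these cases.

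**The case against.** **The wording points to new events.** A reader might infer that the protocol orders pre-existing abnormalities to be counted. It does not. Sections 8.3.1 and 12.2.2 4) speak of events that occurred from the start of treatment and of patients who developed them, and the ordinary sense of both is onset after first dose. This stands. The text leaves ongoing and worsening conditions undefined, so sites may differ in what they enter.

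**Laboratory baselines exist.** A reader might also infer that there is no baseline at all, so that anaemia or raised liver enzymes are bound to be miscounted. The two sets of pre-dose blood tests contradict this. Whether the values allowed at entry reach grade 2 depends on grading cut-offs that the protocol does not reproduce, so the point does not rest on them.

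**Carry-over is not automatic.** A third inference is that toxicity unresolved at a switch is always scored to the second drug. Section 8.3.1 follows related or severe events as far as possible until they resolve or stabilise, so their follow-up under the first drug need not end at the switch. Section 6.1 also asks for an appropriate interval from the previous treatment. Both reduce the problem. Neither keeps the same unresolved condition out of the second drug's worst-grade count.

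**Other documents may help.** A rule for treatment-emergent events is normal analysis plan content, and its absence here is no finding. The protocol also refers to an EDC input manual and separate safety procedures, which were not available, and a form could go beyond what the protocol asks. But a counting rule cannot supply symptom grades that nobody was required to record.

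**Consequences are limited.** The study is exploratory and has no comparative safety test, and the numerical safety trigger in 12.7.1 uses treatment-related deaths. This stands, and it limits the weight of the point.

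**Conclusion.** The point holds for non-laboratory conditions. The protocol requires no pre-dose grade for them and builds a per-drug incidence, regardless of cause, from the worst grade after first dose. Conditions present at first dose, including toxicity left over from an earlier cohort, can therefore be counted as events of the current drug, and later analysis of the required data cannot undo that.

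If such conditions are entered, the incidence is overstated. The size is unknown. The 14.5% to 28.0% against a true 10% rests wholly on assumed prevalences of 5% to 20%, on independence, and on every such condition being entered. It shows what is possible, not what happened. No figure in the protocol is contradicted. This is a cheap improvement to a secondary endpoint and does not touch the primary analysis.

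**What to change.** 1. In section 8.6, add a required entry in the start-of-treatment column, for each enrollment, recording any ongoing condition and its grade before first dose. A patient who re-enrols under 2.7 gets a fresh entry.
2. Derive baseline laboratory grades from the tests that 8.2.3 already requires, and state that these values are entered in the EDC.
3. In sections 12.2.2 4) and 12.3.3, count an event only if it is new, or rises above its pre-dose grade, after the first dose of that cohort's drug. Give the uncorrected worst-grade table as a supplement.

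The cost is slightly more data entry at sites, one change to the form and a few lines of text. No new visit or test is needed. The entry has to be made prospectively. Patients who have already started treatment could at best be completed from the chart, and should be marked as such.
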